# Groups for belonging: a parallel cluster randomized controlled trial of a group-based loneliness intervention for people attending treatment for alcohol and other drug use

**DOI:** 10.1186/s12889-025-24369-6

**Published:** 2025-08-27

**Keywords:** Loneliness, Belonging, Intervention, Substance use, Experience, Satisfaction, Randomized controlled trial

## Abstract

**Background:**

People accessing alcohol and other drug (AOD) treatment experience high rates of loneliness, which is a strong driver of substance use. Groups for Belonging is a 6-session group-based intervention that combines elements of the social identity informed intervention Groups for Health with psychoeducation and strategies to help participants manage loneliness and overcome cognitive barriers to social connection. The project will examine the effectiveness and cost-effectiveness of delivering *Groups for Belonging* within routine care offered by AOD treatment providers in Australia.

**Methods:**

Participants will be adults attending residential or community-based AOD treatment provided by either public sector or non-government treatment providers across New South Wales (NSW), Victoria (VIC), Queensland (QLD) and the Australian Capital Territory (ACT) in Australia. The study will be conducted as a parallel cluster randomized controlled trial (RCT), involving 26 clusters (13 treatment, 13 control, *N* = 520), with randomization occurring at the service level. Depending on randomization, participants will either complete treatment as usual (i.e., AOD treatment provided by participating services) or Groups for Belonging and treatment as usual.

**Discussion:**

This study aims to determine the effectiveness of a loneliness intervention, *Groups for Belonging*, for people accessing residential and community-based treatment for AOD use. If the intervention is effective and cost-effective, implementation efforts will focus on embedding the intervention into routine care in AOD treatment services across metropolitan and regional areas in Australia. This has significant potential to decrease loneliness and its associated effects on health and wellbeing for people accessing AOD treatment.

**Trial registration:**

Australia and New Zealand Clinical Trials Registry, CTRN12625000132448 (https://www.anzctr.org.au/ACTRN12625000132448.aspx). Registered on 6 February 2025.

**Supplementary Information:**

The online version contains supplementary material available at 10.1186/s12889-025-24369-6.

## Background

Loneliness is a public health priority. It is estimated that up to 25% of the population experience loneliness, with estimated rates rising worldwide, and impacting people of all ages [1]. Although widespread, we are not ‘all in the same boat’ when it comes to loneliness. Those who have poorly-met financial needs are 2.8 times more likely to be lonely (51%) than those with well-met financial needs (27%) [2]. In Australia, 39% of those living in the most disadvantaged communities report being lonely, compared to 28% of those in the least disadvantaged neighborhoods [2]. Often falling in the lower socioeconomic band, people accessing treatment for alcohol and other drug (AOD) use are seven times more likely to experience loneliness and perceived their loneliness to be five times more serious than people in the general population [3]. Loneliness is a significant predictor of poor physical and mental health, and increased morbidity and mortality rates [4]. People accessing treatment for AOD use experience poor health and an increased propensity to chronic diseases [5]. The high rates of loneliness observed across people accessing AOD treatment are likely to contribute to further health disparities in this population.

A review of 41 studies examining loneliness in people with problematic AOD use found loneliness was associated with poor physical and mental health, as well as an increased frequency, severity and duration of substance use amongst this population [6]. The review also identified that targeted loneliness interventions that meet the specific social needs of this population are lacking. Only one intervention had been trialed with people accessing AOD treatment and it found the intervention had no effect in reducing loneliness relative to control [7]. The study was conducted four decades ago, and the intervention was broad in scope, highlighting a need for more up to date, targeted interventions. People who are accessing AOD treatment experience unique social challenges as substance use is typically a key part of the social network when they enter treatment, but once they reduce, or are no longer using substances, their social needs change. No longer identifying as strongly with substance using social groups when addressing AOD use can trigger feelings of isolation, making treatment engagement a particularly vulnerable time for these individuals [8, 9].

There are key cognitions and behaviors that contribute to, and maintain, loneliness for people who use AOD to a problematic extent. A qualitative study with people accessing AOD treatment found that mistrust, perceived lack of support from others, low self-worth, fear of negative evaluation, poor quality and authenticity in relationships, and unhelpful interpersonal behaviors were both key contributors to, and consequences of, loneliness [10]. Additionally, participants identified that their substance use contributed to feelings of loneliness and that these feelings led to engaging in, or re-engaging in, problematic AOD use [10]. In this study, participants indicated that support groups, identifying and pursuing authentic relationships and engaging in activities that provide a sense of purpose would likely help appease feelings of loneliness. In response to this need and the study’s findings, a novel loneliness intervention, *Groups for Belonging*, was developed (see [11]).

*Groups for Belonging* is a 6-session (2-hours per session) group-based intervention that is based on a social identity approach to health as well as cognitive theories of loneliness. The social identity approach suggests that the groups and communities that we belong to help to shape our identity and sense of belonging, and that loneliness is a result of a loss or lack of group memberships and identities. *Groups for Belonging* adapts some elements from the social identity informed intervention, Groups for Health [12], an evidence-based intervention for socially isolated adults that has been examined using both proof of concept and RCT study designs. Groups for Health has demonstrated reductions in loneliness and related distress amongst university students and adults accessing mental health services in Australia [12, 13]. *Groups for Belonging* uses some elements from Groups 4 Health such as psychoeducation about the influence of social connections on health, and a personalised mapping of social groups.

In addition, cognitive theories suggest that the way we think of ourselves and others in relationships guides the way we will interact and behave in relationships, which in turn will determine how connected we feel to others [14]. *Groups for Belonging* aligns with cognitive theories of loneliness by helping participants to identify and address cognitive barriers to social connection such as stigma, social anxiety and difficulty trusting others (see [10]). A feasibility trial (*N* = 41) of *Groups for Belonging* in residential AOD treatment services revealed high levels of satisfaction with the program, with 89% reporting the highest possible satisfaction rating [15]. While the study was underpowered to detect significant effects of the intervention on loneliness and related outcomes, it pointed to a need for an adequately powered RCT to determine the effectiveness of *Groups for Belonging* for people accessing treatment for AOD use.

## Objectives

This study will examine the effectiveness and cost-effectiveness of delivering *Groups for Belonging* within routine care offered by AOD treatment service providers in Australia. It is hypothesized that compared to treatment as usual, *Groups for Belonging* will be associated with greater reductions in loneliness (primary outcome variable). Secondary outcomes will examine cost effectiveness, the impact of group participation on substance use, social group membership, physical health, mental health, and wellbeing.

## Methods

### Design

The study will be conducted as a parallel cluster-RCT, involving 26 clusters (13 treatment, 13 control), with randomization occurring at the service level. Depending on randomization, participants will either complete *treatment as usual* (TAU; i.e., treatment for AOD use provided by participating services) or *Groups for Belonging* and treatment as usual. Assessments will be conducted at baseline, 7-weeks (post intervention), and 31-weeks (6-months post-intervention). Assessment officers, blind to treatment condition, will collect the primary and secondary outcome measures at each of these timepoints. The study design was developed in consultation with a lived experience advisor, as well as multiple Consumer Advisory Groups and these consultations will occur throughout the duration of the project. The protocol follows Standard Protocol Items: Recommendations for Interventional Trials (SPIRIT) guidelines (see Supplementary File 1 SPIRIT checklist). Figure 1 describes the study flow.

**Fig. 1 Fig1:**
[figure not shown]
Flow chart of study procedure

### Setting

Participants will be attending residential or community-based programs provided by either public sector or non-government AOD treatment providers across the Australian states of New South Wales (NSW), Victoria (VIC), Queensland (QLD) and the Australian Capital Territory (ACT). The programs offered by each of these services will be diverse, however, all services will offer AOD treatment programs that are accessed by participants for a minimum of 5-weeks. Recruitment of the trial sites will be facilitated by the peak bodies for non-government services across those states, and through consultation with state provided public health services. To promote the generalizability of findings, sites will be located across metropolitan and regional areas of Australia.

### Participants

A total of 520 adults will be recruited to participate in the study and will be involved in either the treatment (Groups for Belonging, *n* = 260) or control (treatment as usual, *n* = 260) condition depending on which condition the site that they are accessing has been randomly allocated to.

#### Inclusion and exclusion criteria

Participants will be required to: (i) be an adult (aged 18 + years) currently accessing treatment for AOD use (i.e., not for gambling); (ii) have a current interest in improving social connections; (iii) intend to access treatment for at least 5-weeks; and (iv) have access to a mobile telephone to complete follow-up assessments. Exclusion criteria will be kept to a minimum to promote the generalizability of the findings. Participants will be excluded from the study if they are currently experiencing acute suicidality or unstable mental health symptoms as determined by themselves, their case workers, or the research clinicians.

### Randomization

The randomization procedures will be managed by an independent statistician based at the Hunter Medical Research Institute (HMRI). Block randomization will be used to randomize clusters to each arm in a 1:1 ratio. Randomization will be stratified by service type (residential or community) to ensure balance of service types across the study arms. Treatment as usual will be used as the comparator condition to ascertain whether the intervention (*Groups for Belonging*) is effective above and beyond the standard services offered within the AOD treatment services setting.

### Conditions

#### Treatment condition (Groups for belonging and TAU)

Participants allocated to the treatment condition will complete treatment as usual in addition to completing Groups for Belonging [17]. Groups for Belonging involves 6 × 2-hour sessions (*n* = approximately 10 participants per group) delivered over a 4 to 6-week period, depending on the length of the program offered by respective treatment sites (i.e., up to 2 sessions can be delivered per week where necessary). *Groups for Belonging* is based on cognitive theories of loneliness, which posit that unhelpful cognitions act as barriers to connection [14], and a social identity approach which suggests that identification with social groups enhances connection and belonging [18, 19]. The program aims to help participants understand the connection between loneliness and substance use, identify relationships that might be barriers or facilitators to their AOD treatment goals, to identify and manage the cognitions (e.g., stigma, mistrust, fear of negative evaluation, fear of showing feelings) that act as barriers to connection, and to develop goals and strategies that help to promote positive social connections. Figure 2 outlines the key aspects of the *Groups for Belonging* program.

**Fig. 2 Fig2:**
[figure not shown]
Session outline of groups for belonging

#### Control condition (TAU)

Participants allocated to the control condition will continue with treatment as usual (the AOD treatment program offered by the community/residential service that they are attending).

### Recruitment

Study information (e.g., flyers, posters, and participant information sheets) will be available at each treatment site. Research clinicians will also visit the sites to meet with potential participants to discuss the study. Alternatively, staff of the treatment services will provide the research officers with the names and contact details of potentially interested consumers. At each site, potential participants will be asked to complete a brief expression of interest form. On this form, the eligibility criteria will be outlined. If participants are interested in the project, the research clinician will contact the consumer via telephone, or in person where practicable, and provide more information about the study, review the eligibility criteria, and complete the informed consent procedures.

### Participant retention

Participant retention will be facilitated by obtaining detailed contact information and multiple secondary contacts. Research clinicians will attend the treatment services to facilitate follow-up data collection and promote retention in the study. For each assessment completed, participants will be reimbursed with an AUD$50 cash, gift card or direct debit into their nominated bank account, according to participant preference. Text message reminders will also be sent to participants 48 h prior to their scheduled follow-up assessments.

### Trial monitoring

#### Intervention delivery–training and supervision

Research clinicians will be employed to facilitate the *Groups for Belonging* intervention onsite at each of the AOD treatment services involved in the project. These clinicians will complete formal training led by the developers of the intervention, who are experienced clinical psychologists (II and GD). The intervention will be co-facilitated by a nominated staff member of each AOD treatment service. The clinical psychologists will also provide weekly supervision and coaching to research clinicians and treatment service staff delivering the intervention.

#### Treatment fidelity

A clinical psychologist and experienced researcher ([name]) will oversee the training and supervision of fidelity assessors. *Groups for Belonging* sessions will be audio recorded, and the trained Fidelity Assessor will rate a random allocation of 20% of treatment sessions (stratified by session and study site) for adherence and competence. Instruments used to measure fidelity and competence were developed and selected using steps outlined by Walton, Spector [20]. A fidelity checklist was developed using the Behavior Change Technique Ontology [21] to accurately capture the content of the *Groups for Belonging* sessions. The manualized group intervention check [22] was selected to capture clinician competence using a 30-item instrument.

#### Adverse events

Auditing of trial conduct will be undertaken by the trial coordinator (EC). Adverse events will be recorded by clinical researchers and assessment officers and managed by the trial coordinator (EC) throughout the duration of the trial according to specific steps approved by the overseeing ethics committee (Royal Prince Alfred Hospital HREC; 2024/ETH00914). Necessary steps will be taken to ensure participants are linked in with appropriate services and support.

### Data collection

Demographic characteristics including date of birth, age, postcode, gender, identification as Aboriginal and/or Torres Strait islander, marital status, sexual orientation, dependents/children, living situation, accommodation, education level, employment, job status, history of treatment for AOD use, history of mental and/or physical health conditions, and use of medications will be collected at baseline. All primary and secondary outcomes will be collected at baseline, 7-weeks (i.e., post intervention) and 31-weeks (i.e., 6-months post intervention) and entered directly into Research Electronic Data Capture (REDCap) platform using a laptop (see Table 1). Baseline assessments will be completed either via telephone or, where possible, onsite at the AOD treatment services. Blinded assessment officers will collect the primary and secondary outcome measures via telephone at all timepoints, while research clinicians will collect all other measures at baseline as a means of building rapport with participants. The blinded assessment officers will be trained in the administration of the outcome measures and will receive weekly supervision with one of the senior team members (TD). The assessments will be reviewed weekly for completeness to minimize missing data and improve accuracy. As part of the baseline assessment procedure, contact details for the participant and a nominated alternate contact will be collected to facilitate completion of the follow-up assessment procedures.

### Follow-up

Follow-up will be conducted via telephone at 7-weeks after baseline and again at 6-months post-intervention. To ensure blind assessment of outcome measures, the primary and secondary dependent measures will be collected by an assessment officer who is naïve to allocation and study design. At the beginning of each phone call, participants will be reminded that they should not reveal their condition to the assessment officer. If participants disclose their condition, an alternative assessment officer will complete the assessment. Assessments will take approximately 30 min to complete. Multiple methods will be used to stay in contact with participants (e.g. telephone, email, SMS, social media). Alternate contact details provided by the participant will be used if there is difficulty reaching the participant. Table 1 reflects a schedule of assessments, including the primary and secondary outcomes collected at each time point.

**Table 1 Tab1:** Schedule of assessments

Domain	Data		Assessment Interval			
		Pre-Trial	Baseline	Intervention period	7-w	6-m
Recruitment	Eligibility	x ^c^				
Demographics						
	Date of Birth		x^b^			
	Age		x^b^			
	Postcode		X^b^		x^a^	x^a^
	Gender		X^b^			
	Aboriginal and/or Torres Strait Islander		x^b^			
	Marital status		x^b^			
	Sexual orientation		x^b^			
	Dependents/children		x^b^			
	Living arrangements		x^b^			
	Accommodation		x^b^			
	Education		x^b^			
	Employment		x^b^			x^a^
	Job status		x^b^			
	Previous treatment episode		x^b^			
	Mental health diagnoses		x^b^			
	Physical health conditions		x^b^			
	Medications		x^b^			x^a^
Substance use						
	TLFB (i.e. days of use)^2^		x^a^		x^a^	x^a^
	Treatment goals		x^b^		x^a^	x^a^
	Cravings (DAQ-6)^2^		x^a^		x^a^	x^a^
Loneliness						
	Single item		x^b^			
	Drinking Motivations		x^b^			
	UCLA (Version 3)^1^		x^a^		x^a^	x^a^
Social variables						
	Multiple group membership^2^		x^a^		x^a^	x^a^
	SEMSI		x^b^		x^a^	x^a^
	Use/recovery identity		x^b^		x^a^	x^a^
	Support for treatment goals		x^b^		x^a^	x^a^
Barriers to connecting						
	Self-stigma		x^b^		x^a^	x^a^
	Mini-SPIN		x^b^		x^a^	x^a^
	Young Schema Questionnaire (mistrust, emotional inhibition, defectiveness/shame)		x^b^		x^a^	x^a^
Wellbeing						
	Psychological health (K10)^2^		x^a^		x^a^	x^a^
	Suicidality (CSSRS-S)		x^a^		x ^a^	x ^a^
	Quality of life (AQoL-8D)^2^		x^a^			x^a^
Experience of Care						
	YES				x^a^	
	PREMAT				x^a^	
Service use						
	CSRI^2^		x^a^			x^a^
	Travel^2^		x^b^	x^c^	x^a^	
G4B experience (treatment arm only)						
	Group Climate Questionnaire				x^c^	
	8-item program evaluation				x^c^	

^a^Assessment done via telephone with blinded Assessment Officer or via electronic link. ^b^Assessment done with research clinician. ^c^Completed independently by participant. ^1^Primary Outcome. ^2^Secondary outcomes. *TLFB* Timeline Follow Back, *DAQ-6* Desires for Alcohol Questionnaire, *UCLA* University of California Los Angeles Loneliness Scale, *SEMSI* Self-Efficacy in Managing Social Identities, *Mini-SPIN* Mini Social Phobia Inventory, *K10* Kessler 10, *AQoL-8D* Assessment of Quality of Life – 8 Dimensions, *YES Survey* Your Experience of Service Survey, *PREMAT* Patient Reported Experience Measure for Addiction Treatment, *CSRI* Client Services Receipt Inventory, *G4B* Groups for Belonging

### Primary outcome

#### Loneliness

The 20-item UCLA Loneliness Scale (Version 3) [23] will be used. This is the most widely used and robust loneliness measure. It has been recommended for people experiencing mental health conditions, over the abbreviated versions of this scale [24]. This scale has been designed to measure an individual’s subjective feelings of loneliness. An example item is “How often do you feel that no one really knows you well”. Response options include: 1 - never, 2 - rarely, 3 - sometimes or 4 - often. A total score is computed, and higher scores indicate greater loneliness [25].

### Secondary outcomes

#### Days of substance use

The Timeline Follow back (TLFB) method will be used to obtain information about duration of abstinence and days of substance use. The TLFB is the “most psychometrically sound” self-report measure of substance use [26, 27]. Participants are presented with a calendar and are asked to provide retrospective data on their days of substance use over a 28-day period prior to their treatment entry [26].

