#### Data analysis

Statistical analyses will be managed by independent statisticians. Loneliness scores will be analyzed using linear regression in a mixed modelling framework. Fixed effects will include terms for intervention, time point (7 weeks or 6 months), an interaction between intervention and time point, baseline loneliness score, and strata (community-based vs. residential), and random effects for cluster and participant will be included to account for clustering by site, and repeated measurements on participants. The estimated mean difference in loneliness scores between the arms at the primary (6 months) and secondary (7 weeks) time points will be reported, along with 95% confidence intervals, and p-values, as summary measures of the intervention effectiveness.

The analysis set for the primary outcome will be Intention to Treat, however, sensitivity analyses using the Per Protocol analysis set will also be performed. In the case of missing data, multiple imputation methods will be utilized to ensure the analysis set is Intention to Treat. Analysis of secondary outcomes at 7 weeks and 6 months will also utilize linear mixed models (if assumptions of normally distributed residuals and constant variance are met) or generalized linear mixed models otherwise. Fixed effects will include those listed above for the primary outcome variable. Effect estimates for the difference between arms, 95% confidence intervals, and p-values, will be reported for each outcome at each follow-up time point. A sub-group analysis will be performed estimating the difference in change in loneliness from baseline among those participants who reported high loneliness scores at baseline. A secondary sub-group analysis comparing the difference in loneliness scores at 7 weeks and 6 months for residential participants compared to community-based participants will also be performed.

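### The only recall window stated for the TLFB days-of-use outcome ends at treatment entry and is not limited to baseline, although the outcome is compared between arms at 7 weeks and 6 months

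*Protocol article*

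**What the plan says.** All references are to the protocol article.

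- **Days of substance use** (under Secondary outcomes). The TLFB "will be used to obtain information about duration of abstinence and days of substance use". Participants are "asked to provide retrospective data on their days of substance use over a 28-day period prior to their treatment entry". This is the only recall window given for the instrument.
- **Table 1** (under Follow-up). The row "TLFB (i.e. days of use)^2" carries the secondary-outcome footnote and is marked at baseline, 7 weeks and 6 months.
- **Data collection.** "All primary and secondary outcomes will be collected at baseline, 7-weeks (i.e., post intervention) and 31-weeks (i.e., 6-months post intervention").
- **Follow-up.** "Follow-up will be conducted via telephone at 7-weeks after baseline and again at 6-months post-intervention".
- **Data analysis.** "Analysis of secondary outcomes at 7 weeks and 6 months" uses mixed models with the same fixed effects as the primary model, and a between-arm estimate is reported for each outcome at each follow-up.
- **Objectives.** The effect of group participation on substance use is named among the secondary outcomes.

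**The concern.** A recall window tied to treatment entry suits a baseline measurement. The same measure is also scheduled and analysed as a follow-up outcome, and the article gives no window that moves with the assessment date. If the stated window were used at each call, participants would be asked three times about the same month before treatment.

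That quantity is settled before any group session. An arm difference in it could come only from differential recall or from imbalance between arms. A null result could then be read as showing no effect on substance use when later use had not been measured. The link between loneliness and substance use is part of the trial's rationale, so this secondary outcome needs a definition that can carry the comparison planned for it.

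**Working it through.** The plan gives no figure for this point. The check is one of dates.

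**Inputs**

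- Stated window: 28 days ending at treatment entry (Days of substance use).
- Entry relative to enrolment: participants must be "currently accessing treatment for AOD use (i.e., not for gambling"), so entry is no later than baseline (Inclusion and exclusion criteria).
- Assessments: 7 and 31 weeks after baseline (Design; Data collection; Follow-up).
- Days from entry to baseline, *b*: not given. I assume 0, 7, 14 and 28 to show the range.

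**Formulas.** Take treatment entry as day 0. The stated window is days −28 to −1. Baseline is day *b* ≥ 0. The assessment at week *w* falls on day *b* + 7*w*. The gap from the last day of the window to the assessment is (*b* + 7*w*) − (−1) = *b* + 7*w* + 1.

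**Results**

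| *b* (assumed) | Window days after baseline | Gap to 7-week assessment | Gap to 31-week assessment |
|---|---|---|---|
| 0 | 0 | 0 + 49 + 1 = 50 days | 0 + 217 + 1 = 218 days |
| 7 | 0 | 57 days | 225 days |
| 14 | 0 | 64 days | 232 days |
| 28 | 0 | 78 days | 246 days |

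The zero does not depend on *b*: a window that ends on day −1 cannot contain a day on or after day *b* ≥ 0.

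**Consequence for the model.** The secondary models take over the primary model's fixed effects, which include the baseline score. I read this as the outcome's own baseline value. Under the literal window, baseline and follow-up values are then repeated recalls of one quantity, and the model would adjust for the thing it analyses.

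**Consequence for abstinence.** The same paragraph says the TLFB is to provide abstinence duration. A window that closes at entry can say nothing about abstinence after entry.

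**A window tied to the assessment.** With *b* = 0, the 28 days before each assessment are days 21–48 and days 189–216, all after baseline. The groups are "delivered over a 4 to 6-week period, depending on the length of the program offered by respective treatment sites". If they began on day 0 (an assumption), delivery would run to day 27 (4 weeks) or day 41 (6 weeks). The 7-week window would then include 7 to 21 days of delivery, and the 31-week window would lie wholly after it.

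**Primary outcome and sample size.** The power calculation concerns loneliness only. With 20 × 0.70 = 14 analysed per cluster, the design effect is 1 + 13 × 0.05 = 1.65. The effective size is 13 × 14 / 1.65 = 110.3 per arm. A noncentral t calculation with 24 degrees of freedom and two-sided 5% (sidedness is not stated) gives 81.3%, against the stated 81%. No term in it involves the TLFB.

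**The case against.** The strongest reply is that the article never says the pre-entry window is used at follow-up. The sentence reads as a general description of the instrument, probably written with the baseline administration in mind. The rest of the article points to follow-up use as the intended quantity: the objective, the repeated rows in Table 1, the models at both follow-ups and the mention of abstinence. Visit-specific recall windows are also a detail that a condensed article may leave to the full protocol or case report form. The Client Service Receipt Inventory, for example, is given at two time points with no look-back period.

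Much of this stands. A reader might infer that the substance-use outcome is certain to be lost, or that the investigators chose an analysis that cannot detect an effect. The documents support neither. The loss is conditional on literal use at follow-up, and the follow-up form is not shown. Nor does this inconsistency by itself support adding further items, such as a record of days spent in residential care. That is a separate design question.

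What does not stand is treating the matter as mere omission. Silence about the window would be excusable. Here the article states a window, without restriction, that does not fit its own schedule and analysis, and no other section repairs it. The K10 description shows the contrast: its example item asks about the past 4 weeks, a period that moves with the assessment.

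**Conclusion.** The point holds as a fault in the definition of one secondary outcome. As written, the days-of-use window contains none of the post-baseline period, while the outcome is collected and compared between arms at 7 and 31 weeks. If the sentence were followed exactly at follow-up, those values could not respond to the intervention. If it is not followed, the published definition is wrong for two of the three time points, and readers cannot tell what the reported days of use represent.

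The zero overlap rests only on treatment entry being no later than baseline, which the eligibility criteria imply. The gaps of 50 to 78 and 218 to 246 days rest on the assumed entry-to-baseline interval. The primary outcome, its model and the sample size are untouched. This should be fixed, but it does not threaten the trial's main conclusion.

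**What to change.** In the Days of substance use paragraph, limit the pre-entry window to the baseline assessment. State that at 7 and 31 weeks the TLFB covers the 28 days immediately before the assessment date. Check that the follow-up data-collection form uses the same window, and correct it only if it does not.

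The cost is about one sentence and one check of the form. No visits, participants or model terms change, and the pre-entry baseline value can still serve as the covariate. It should be settled before follow-up data are collected under the present wording, because a month that was never asked about cannot be recovered in the analysis.
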